## 5. SUBJECT POPULATION

Patients must meet all of the inclusion criteria and none of the exclusion criteria to be eligible for this trial. There will be no exceptions made to these eligibility requirements at the time of randomisation. All enquiries about eligibility should be addressed by contacting the regional site coordinating centre prior to randomisation.

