# ALT GIST

7. Adequate bone marrow function (Haemoglobin  $\geq 9.0\text{g/dL}$ , platelet count  $\geq 100 \times 10^9/\text{L}$ , and absolute neutrophil count  $\geq 1.5 \times 10^9/\text{L}$ ).
8. Adequate liver function (Serum total bilirubin  $\leq 1.5 \times \text{ULN}$ , INR  $\leq 1.5$ , and ALT, AST, ALP  $\leq 2.5 \times \text{ULN}$  ( $\leq 5 \times \text{ULN}$  for participants with liver metastases)).
9. Adequate renal function (Creatinine clearance  $> 50\text{ml/min}$ ) based on either the Cockcroft Gault formula, 24 hour urine or Glomerular Filtration Rate (GFR scan); and serum creatinine  $\leq 1.5 \times \text{ULN}$ .
10. Tumour tissue available for central review.
11. Willing and able to comply with all study requirements, including treatment timing and/or nature of required assessments.
12. Study treatment both planned and able to start within 14 days of randomisation.
13. Signed, written informed consent.

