# ALT GIST

telithromycin, voriconazole) or strong CYP3A4 inducers (eg carbamazepine, phenobarbital, phenytoin, rifampicin, St John's wort).

20. History of another malignancy within 5 years prior to registration. Patients with a past history of adequately treated carcinoma-in-situ, basal cell carcinoma of the skin, squamous cell carcinoma of the skin, or superficial transitional cell carcinoma of the bladder are eligible. Patients with a history of other malignancies are eligible if they have been continuously disease free for at least 5 years after definitive primary treatment.
21. Pregnancy, lactation, or inadequate contraception. Women must be post menopausal, infertile, or use a reliable means of contraception. Women of childbearing potential must have a negative pregnancy test done within 7 days prior to registration. Women of childbearing potential and men must agree to use adequate contraception before entering the trial until at least 8 weeks after the last study drug administration.

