### 6.2. Randomisation

Randomisation will be done according to the instructions in the Study Manual. Participants will be randomly assigned electronically by a computerised system.

Randomisation should be done only after all screening assessments have been performed and the responsible investigator has verified the participant's eligibility.

Randomisation occurs once all the inclusion criteria has been met.

Once the randomisation processes have been completed as per the instructions in the Study Manual, the patient will be assigned a subject study number, a treatment arm, and confirmation of successful randomisation is provided to the site.

Individuals may only be randomised once in this trial.

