## ALT GIST

### 8. ASSESSMENT PLAN

#### 8.1. Schedule of assessments

Assessments must be completed within 3 days of the assessment due date (unless otherwise specified in the footnotes)

**ARM A IMATINIB ALONE** NB: 1 cycle in continuous treatment arm = 8 weeks of imatinib (56 days)

| Parameter                                        | Screening/
Baseline
(28 days prior to
randomisation) | Cycle 1        |         | Cycle 2 |         | Cycle 3 |         | Cycle 4 and ongoing
cycles         | 30 day
safety
assessment | Follow-up (12 weekly)                          |
|--------------------------------------------------|---------------------------------------------------------------|----------------|---------|---------|---------|---------|---------|---------------------------------------|--------------------------------|------------------------------------------------|
|                                                  |                                                               | Wk 1D1         | Wk 4 D1 | Wk 1D1  | Wk 4 D1 | Wk1 D1  | Wk 4 D1 | Wk1 D1                                |                                |                                                |
| Informed consent                                 | x a                                                |                |         |         |         |         |         |                                       |                                |                                                |
| Pregnancy test                                   | x                                                             | x d |         |         |         |         |         |                                       |                                |                                                |
| Clinical assessment b                 | x                                                             | x              | x       | x       | x       | x       | x       | x                                     |                                |                                                |
| Mutation status if not
previously determined  | x c                                                |                |         |         |         |         |         |                                       |                                |                                                |

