b: clinical assessment including vital signs, blood pressure, physical examination, ECOG PS,

c: analysis of tumour mutation status if not previously known does not need to be completed prior to randomisation

d: if screening bloods and urine tests are performed within 14 days prior to randomisation baseline bloods and urine are not required to be repeated

e: biochemistry including serum creatinine, urea, LFT, TFT, calcium, magnesium, phosphate. INR should be checked at baseline and then as clinically indicated

f: full blood count including differential cell count

g: dipstick urinalysis using standard urine test strip is required on D1 of each cycle. If abnormal, further investigations should be conducted as clinically appropriate

h: blood collected for drug (imatinib) level testing. Refer to Biological Sampling Handbook for details of collection and processing. Documentation of compliance with treatment during the preceding cycle should be documented in the eCRF

i: blood for **optional** translational research will be collected at these timepoints. Refer to Biological Sampling Handbook for details of collection and processing

j: for the first 12 months, CT scans are performed 8 weekly from randomisation after which CT scans are performed 12 weekly. Imaging of the brain should be undertaken if clinically indicated. CT scans should continue as per the protocol until PD

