| Informed consent                                 | x a                                                   | If patient is
on Imatinib
therapy for
longer than
21 days
prior to
randomisati
on a
washout
must occur.
Imatinib
must stop
for a
minimum of
3 days prior
to starting
regorafenib
on D29 . |                |                            |                |                      |                |                            |                |                      |                    |                                    |                             |                          |
| Pregnancy test                                   | x                                                                |                                                                                                                                                                                                                                              | x d |                            |                |                      |                |                            |                |                      |                    |                                    |                             |                          |
| Clinical assessment b                 | x                                                                |                                                                                                                                                                                                                                              | x              |                            | x              |                      | x              |                            | x              |                      | x                  | x                                  |                             |                          |

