| PET Scan n                            |                                                                  |                                                                                                                                                                                                                                              |                |                            |                |                      |                | x                          | x              |                      |                    |                                    |                             |                          |
| -Imatinib washout
or PET Scan n    |                                                                  |                                                                                                                                                                                                                                              |                |                            |                |                      |                |                            |                |                      |                    |                                    |                             |                          |
| -Regorafenib washout                             |                                                                  |                                                                                                                                                                                                                                              |                |                            |                |                      |                |                            |                | x                    | x
Wk1 D1 only   |                                    |                             |                          |

a: up to 90 days prior to randomisation

b: clinical assessment including vital signs, blood pressure, physical examination, ECOG PS

c: analysis of tumour mutation status if not previously known does not need to be completed prior to randomisation

d: if screening bloods and urine test are performed within 14 days prior to randomisation baseline bloods and urine tests are not required to be repeated

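### Footnote d waives the Day 1 pregnancy test for every woman who meets the 7-day entry rule, so a first dose can come 21 days after the last negative test

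*Protocol*

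**What the plan says.** Four rules in the protocol bear on when pregnancy is tested relative to treatment.

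- **Entry.** Section 5.3, criterion 21: "Women of childbearing potential must have a negative pregnancy test done within 7 days prior to registration". Section 6 describes no separate registration step.
- **Schedule.** In section 8.1 the "Pregnancy test" row of each arm's table has two entries: one in a screening column that reaches back 28 days before randomisation, and one at Cycle 1 Week 1 Day 1. The Day 1 entry is marked with footnote d in both arms. Neither table lists a later pregnancy test.
- **Waiver.** Footnote d for Arm A: "if screening bloods and urine tests are performed within 14 days prior to randomisation baseline bloods and urine are not required" to be done again. Arm B has the same waiver, on the same condition: "if screening bloods and urine test are performed within 14 days prior to randomisation".
- **Start of treatment.** Section 5.2, inclusion criterion 12: "Study treatment both planned and able to start within 14 days of randomisation".

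Eligibility is binding. Section 5 states: "There will be no exceptions made to these eligibility requirements at the time of randomisation". Section 6.2 adds: "Randomisation should be done only after all screening assessments have been performed and the responsible investigator has verified" that the patient qualifies. Section 8.1 also sets a general tolerance: "Assessments must be completed within 3 days of the assessment due date (unless otherwise specified in the footnotes").

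**The concern.** The waiver window (14 days) is wider than the entry window (7 days), and both are counted back from the same event if registration means randomisation. The condition for skipping the Day 1 test is then met by everyone who is eligible, and the Day 1 entry has no force. Because treatment may begin up to two weeks after randomisation, the last required negative test can be well out of date at first exposure.

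What is at stake is safety. Section 10.3 requires study drug to be stopped at once if pregnancy occurs, with counselling about the foetus. The scheduled test closest to the first dose is the one the waiver removes, and no other pregnancy test is scheduled after entry. The primary endpoint, the sample size and the analysis are not affected.

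There is a smaller, separate problem. The pregnancy-test rows do not show the 7-day limit. A site working from the schedule alone could accept a test that fails criterion 21.

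**Working it through.** The protocol states no interval from test to first dose, so there is no figure to reproduce. The check is interval arithmetic.

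**Inputs**

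- Oldest test allowed at entry: 7 days before registration (criterion 21).
- Oldest test that triggers the waiver: 14 days before randomisation (footnote d, both arms).
- Latest start of treatment: 14 days after randomisation (inclusion criterion 12).
- Assumption: registration and randomisation fall on the same date. Section 6 has no separate registration step, and section 15 names the two together as a single item.

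**Step 1: does footnote d reach the pregnancy test?** In each table footnote d is attached to three Day 1 cells: pregnancy test, biochemistry and haematology. The Day 1 urine dipstick cell does not carry it. Biochemistry and haematology are blood tests, so the only marked row that the footnote's mention of urine can describe is the pregnancy test. A serum pregnancy test would fall under bloods. The waiver applies either way.

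**Step 2: who is exempt?** An eligible woman's test is at most 7 days old at randomisation. Since 7 < 14, she always meets the waiver condition. No woman who satisfies criterion 21 is required to have the Day 1 test.

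**Step 3: longest permitted gap.** Test to randomisation plus randomisation to first dose: 7 + 14 = 21 days. That is 21 / 7 = 3 times the age that criterion 21 accepts at entry.

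**Step 4: whom it concerns.** Only women not yet on imatinib. Those already taking it had their first dose before randomisation. Section 8.2.1 confirms that treatment-naive patients will be enrolled.

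**Step 5: sensitivity to the registration date.** Suppose registration came k days before randomisation. The entry test could then be 7 + k days old at randomisation. The waiver would still cover every eligible woman while 7 + k ≤ 14, that is k ≤ 7. The longest gap under the waiver would be 7 + k + 14 = 21 + k days, up to 14 + 14 = 28 days. The assumption therefore gives the shortest version of the gap.

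**Step 6: the schedule read alone.** A screening test on days -15 to -28 would at least trigger the Day 1 repeat. One on days -8 to -14 would trigger none, yet it fails the 7-day rule.

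**The case against.** The strongest reply is that the protocol relies on contraception rather than repeat testing. Criterion 21 itself requires women who could conceive to use a reliable method, from before entry until at least 8 weeks after the last dose. The whole 21-day gap lies inside that period. Treatment then continues for months with no scheduled pregnancy test, and the first regorafenib dose in Arm B (Day 29) has none either. On this view, an entry test plus contraception is a coherent scheme, and the pre-dose interval is no worse than what follows. This lowers the risk and should be acknowledged. It does not explain why the protocol schedules a Day 1 test and then exempts every eligible woman from it.

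Other points on that side:

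- The 7 days in criterion 21 run to registration, not to first dose. This stands: 21 days breaches no stated limit, and the threefold comparison is only a yardstick.
- Footnote d says a repeat is not required, so sites may still test. True, but the safeguard then depends on local habit.
- Section 8.2.1 lists the pregnancy test apart from bloods and urinalysis, and its note waives bloods only. The narrative is narrower than the schedule, but the footnote mark sits on the pregnancy-test cell in both tables.
- The meaning of registration may be settled in the Study Manual or the European group's appendix, which are not shown. An earlier registration date would leave the gap as long or make it longer.
- Sections 5 and 6.2 already bar a woman with a late test. That is right, and footnote d does not override eligibility. The schedule can still mislead a site that works from it alone.

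**Conclusion.** The point holds. For women of childbearing potential not yet on imatinib, the Day 1 pregnancy test is never required of anyone eligible, and the last required negative test can be up to 21 days old at the first dose with every rule followed. This rests on reading registration as randomisation and on taking the 14 days in inclusion criterion 12 as the latest start. Few women in a trial of about 60 will be affected, contraception is mandatory, and reaching 21 days needs both windows used in full. It is a safety correction that should be made because it is cheap and clear, and it has no bearing on the statistical design.

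**What to change.** - In criterion 21, replace registration with randomisation.
- On the pregnancy-test row of both schedules, show the 7-day limit and remove footnote d.
- For women of childbearing potential not already on imatinib, require a negative test within 7 days before the first dose of study treatment, repeated if the entry test is older than that.
- State that the result must be available before the first dose. Otherwise the general 3-day tolerance in section 8.1 would let the Day 1 test be done after dosing has begun.

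This cuts the longest gap from 21 days to 7. The cost is a wording change to one criterion and one row in each of two tables, and at most one repeat pregnancy test in the few women whose entry test is more than 7 days old when treatment starts.

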## 6. STUDY ENROLMENT

### 6.1. Screening

Written informed consent must be signed and dated by the participant, and signed and dated by the Investigator, prior to any study-specific screening investigations being performed. In CD117 negative patients, entry to the study is conditional on the outcome of the DOG-1 expression at immunohistochemistry or *KIT/PDGFR*A mutational status.

### 6.2. Randomisation

Randomisation will be done according to the instructions in the Study Manual. Participants will be randomly assigned electronically by a computerised system.

Randomisation should be done only after all screening assessments have been performed and the responsible investigator has verified the participant's eligibility.

Randomisation occurs once all the inclusion criteria has been met.

Once the randomisation processes have been completed as per the instructions in the Study Manual, the patient will be assigned a subject study number, a treatment arm, and confirmation of successful randomisation is provided to the site.

Individuals may only be randomised once in this trial.

## 7. TREATMENT PLAN

### 7.1. Administration of study treatments

Participants randomised to standard therapy (Arm A) will receive 400mg (1 x 400mg tablet) orally daily of imatinib, with no washout periods.

Those randomised to the experimental alternating arm (Arm B) will receive:

Imatinib 400mg (1 x 400mg tablet) orally daily for 21 to 25 days, then a 3 - 7 day washout period (no drug). A 3 day washout period is mandated, but up to 7 days break is allowed to maximise tolerability of the regimen, at the discretion of the site investigator. In total, the combined number of days taking imatinib plus the washout period must equal 28 days. This is followed by regorafenib 160 mg (4 x 40mg tablets) orally daily for 21 days, then a 7 day washout period.

# ALT GIST

This combination of imatinib, regorafenib and intervening washout periods will constitute 1 cycle of study treatment (imatinib plus washout period 28 days in total; regorafenib plus washout period 28 days in total; cycle duration 8 weeks (56 days) in total). See diagram below.

It is recommended that regorafenib should be taken orally at the same time each day (preferably after breakfast) and the tablets should be swallowed whole with water after a light low fat meal. The prescribed dose of imatinib should be taken orally, with a meal and a large glass of water to minimise the risk of gastrointestinal disturbances

Missed or vomited tablets cannot be compensated for by treatment at a later date and/or time.

[figure not shown]

Even in participants with a complete response, treatment will continue until progressive disease (PD) or prohibitive adverse events are documented. Participants who cease treatment after receiving at least 2 years of therapy from the time of commencing treatment will not be considered to have failed treatment for toxicity reasons. Surgery will be permitted for participants whose cancer becomes operable during trial treatment at the discretion of the treating team, and participants will be able to continue on study treatment and will continue to be followed for progression free survival post operatively. For patients undergoing surgery, regorafenib should be ceased at least 2 weeks prior to surgery, and recommenced on the basis of clinical judgement. During this period, imatinib could be administered until surgery and for the first 2 weeks after surgery regardless of the study Arm allocation,

Treatment after progression will be according to clinician preference and local institutional guidelines. Crossover from either arm to single agent regorafenib will not be permitted as part of the study.

## 7.2. Dose modifications

### Dose escalation:

Regorafenib dosages will not be increased above 160mg daily.

Dose escalation of imatinib up to 800mg daily will be allowed in both arms for those participants with an identified *KIT* exon 9 mutation. It is recommended in this situation that the patient be escalated first to 600mg for at least 2 weeks prior to further escalation to 800mg. The timing of dose escalation for *KIT* exon 9 mutation patients during the trial is at the discretion of the site investigator.

# ALT GIST

## **Dose reductions and delays:**

Instructions for treatment delays and dose modifications for adverse events are specified below. In general, treatment should be withheld during adverse events of severity G3-4, and not restarted until the adverse event has resolved to G0-1, at the investigator's discretion unless otherwise specified. Day 1 treatment may be delayed for a maximum of 28 days. If the adverse event has not resolved to G0-1 after this delay, then study treatment should be discontinued. Treatment should not be delayed or modified for alopecia of any grade.

Specified dose reductions apply to all subsequent doses of study drug. If a patient experiences several adverse events with differing recommendations, then the modification that results in the longest delay and lowest dose should be used.

Dose modification guidelines differ for each arm of the study (see below). For Arm A, dose modifications are provided for adverse events thought to be attributable to imatinib (Table 2). For Arm B, dose modifications are provided for adverse events specific to regorafenib (hand-foot syndrome, hypertension and hepatic dysfunction)- see Tables 3-5, and separately for general adverse events thought related to either regorafenib or imatinib (including nausea, haematologic abnormalities, fatigue) – see Table 5.

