## ALT GIST

|                                                                         |                |                                                                                                                                                                                                          |
|-------------------------------------------------------------------------|----------------|----------------------------------------------------------------------------------------------------------------------------------------------------------------------------------------------------------|
| participant to be unable to work or perform activities of daily living. |                | resolves to Grade 0-1. When resume treatment, decrease dose by one dose level.                                                                                                                           |
|                                                                         | 2nd occurrence | Institute support measures immediately. Interrupt therapy for a minimum of 7 days until toxicity resolves to Grade 0-1. When resume treatment, decrease dose by one additional dose level b . |
|                                                                         | 3rd occurrence | Discontinue study treatment permanently.                                                                                                                                                                 |

a. More conservative management is allowed if judged medically appropriate by the Investigator.

b. Participants requiring > 2 dose level reductions should discontinue protocol therapy permanently.

c. If toxicity returns to grade 0-1 after dose reduction, dose re-escalation is permitted at the discretion of the investigator.

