**If there is no recovery after a delay of 28 days, treatment will be discontinued permanently.**

For participants who require a dose reduction for grade 2 or 3 rash or hand-foot skin reaction, the dose of study drug may be increased to the starting dose after one full cycle of therapy has been administered at the reduced dose without the reappearance of rash or hand-foot skin reaction > grade 1.

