| Grade 4               | Life-threatening consequences (e.g. malignant hypertension, transient or permanent neurologic deficit, hypertensive crisis)                                              |                                                                                                                                                                                                                             | Discontinue study treatment permanently                                                                                                                                                                                                                                                                                                                                                                                            |

a. Participants requiring a delay of 28 days will be permanently discontinued.

b. If blood pressure remains controlled for at least one full cycle, dose re-escalation is permitted at the Investigator's discretion.

c. Participants requiring > 2 dose level reductions will be permanently discontinued.

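### Dose reductions are stated to be permanent, but Tables 3 and 4 permit re-escalation; for grade 2 skin toxicity the protocol gives three different answers

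*Protocol*

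**What the plan says.** Four places in section 7.2 bear on whether a reduced dose may be raised again.

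- **Section 7.2, Dose reductions and delays.** "Specified dose reductions apply to all subsequent doses of study drug". The sentence carries no exception.
- **Section 7.2.1, Table 3 (skin toxicity), footnote c.** "If toxicity returns to grade 0-1 after dose reduction, dose re-escalation is permitted at the discretion of the investigator". It gives no minimum time at the reduced dose and names no target dose. The footnote is marked on the grade 2 rows and not on the grade 3 rows.
- **Section 7.2.1, paragraph after Table 3.** This covers reductions made for skin reactions of either grade, 2 as well as 3. It says that "the dose of study drug may be increased to the starting dose after one full cycle of therapy has been administered at the reduced dose", provided the reaction has not reappeared above grade 1.
- **Section 7.2.2, Table 4 (hypertension), footnote b.** "If blood pressure remains controlled for at least one full cycle, dose re-escalation is permitted at the Investigator's discretion". It is marked on the first dose reduction for grade 3 hypertension.

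Section 7.1 fixes what a full cycle means: "cycle duration 8 weeks (56 days) in total".

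**The concern.** The general sentence makes a reduction permanent, while three later places allow it to be reversed. For skin toxicity the two permissive texts also differ from each other in timing, in target dose and in the grades they cover. An investigator managing a grade 2 hand-foot reaction can therefore point to protocol text for never re-escalating, for re-escalating as soon as the reaction settles, or for waiting a full cycle.

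What is at stake is regorafenib exposure after a toxicity in Arm B. That is first a safety matter. It also feeds the section 13.3 review, which looks at dose intensity in the experimental arm after 15 patients have had at least two cycles. If exposure partly reflects which sentence a site read, that review mixes the tolerability of the regimen with site practice.

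**Working it through.** The point rests on a comparison of texts. The protocol states no figure for it, so there is none to reproduce.

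**Step 1: the texts by toxicity and grade**

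| Event | General sentence, 7.2 | Table 3 footnote c | Paragraph after Table 3 | Table 4 footnote b |
|---|---|---|---|---|
| Skin, grade 2 | No return | Return at grade 0-1, investigator's discretion, no wait, no target dose | Return to starting dose after one full cycle at the reduced dose without reappearance above grade 1 | Not applicable |
| Skin, grade 3 | No return | Not marked | As for grade 2 | Not applicable |
| Hypertension, grade 3 | No return | Not applicable | Not applicable | Return after at least one full cycle of controlled blood pressure |

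The three-way conflict is confined to grade 2 skin toxicity. Grade 3 skin toxicity and hypertension each have a two-way conflict with the general sentence.

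**Step 2: does the general text open the door to exceptions?** It contains one such phrase, in the instruction on withholding treatment for grade 3-4 events: "not restarted until the adverse event has resolved to G0-1, at the investigator's discretion unless otherwise specified". That governs withholding and restarting. The sentence on the permanence of reductions stands in the next paragraph without it. The general text also has a tie-breaker (longest delay, lowest dose), but it is written for a patient with several adverse events, not for one event that falls under several rules.

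**Step 3: size, by illustration**

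Inputs: regorafenib 160 mg for 21 days per cycle (section 7.1); level -1 is 120 mg (Table 1). Assumptions: regorafenib counted alone; a grade 2 skin reaction reduced to 120 mg from day 8 of regorafenib dosing in cycle 1; no interruption; no missed days; no further reduction.

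Planned dose over two cycles: 2 × 21 × 160 = 6,720 mg.

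- Kept at 120 mg in cycle 2 (general sentence, or paragraph after Table 3): (7×160 + 14×120 + 21×120) / 6,720 = 5,320 / 6,720 = **79.2%**.
- Returned to 160 mg for cycle 2 (possible under footnote c if the reaction is back to grade 0-1 by then): (7×160 + 14×120 + 21×160) / 6,720 = 6,160 / 6,720 = **91.7%**.

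Over two cycles the general sentence and the paragraph after Table 3 give the same figure, because cycle 2 is the first full cycle at the reduced dose. Over four cycles (planned 4 × 21 × 160 = 13,440 mg) all three answers separate:

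- never: (2,800 + 3×2,520) / 13,440 = 77.1%;
- back to 160 mg from cycle 3: (2,800 + 2,520 + 2×3,360) / 13,440 = 89.6%;
- back to 160 mg from cycle 2: (2,800 + 3×3,360) / 13,440 = 95.8%.

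Here 2,800 mg is the cycle 1 dose (1,120 + 1,680), 2,520 mg a full cycle at 120 mg, and 3,360 mg a full cycle at 160 mg.

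**The case against.** The strongest reply is that this is ordinary drafting: a general rule first, with toxicity-specific exceptions in the tables below it. Tables 2, 5 and 6 contain no re-escalation clause, so the general sentence still has a field of use, and the section says that modification guidelines differ by arm. On that reading the hypertension footnote and the rule for grade 3 skin toxicity are simply exceptions. This is a fair reading and it softens those two conflicts. The protocol does not state it, however, and it does not help with grade 2 skin toxicity, where footnote c and the paragraph after Table 3 are equally specific.

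A second reply is that the two skin texts fit together, with footnote c giving permission and the paragraph giving timing and target dose. Both are permissive, and footnote a allows more conservative management. But neither text refers to the other. The paragraph already covers grade 2 as well as grade 3, so this reading leaves footnote c with nothing to add and does not explain why it is marked on grade 2 rows only.

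Three stronger readings are tempting and not supported:

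- **That the hypertension rule clashes with the skin rules.** It concerns a different toxicity, and different conditions for different toxicities are no contradiction.
- **That the ambiguity moves a patient across the 75% line in section 13.3.** In the illustration both two-cycle figures lie above 75%. A grade 3 sequence with a seven-day interruption gives a lower total, but there footnote c is not marked and the paragraph after Table 3 requires a full cycle at the reduced dose, so no text permits 160 mg in cycle 2. A grade 2 path can be made to straddle the line only by adding an interruption and assuming the dose on resumption. Section 13.3 in any case considers changes only if more than 10 patients fall short.
- **That time to treatment failure is altered.** Sections 9.4 and 13.2 define it by stopping treatment, progression, death, toxicity or preference, not by dose level. An indirect effect is conceivable, but the protocol gives nothing from which to size it.

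**Conclusion.** The inconsistency is real and should be corrected. It is sharpest for grade 2 skin toxicity, where three texts give three answers and reading the tables as exceptions to the general rule still leaves two of them in conflict. For grade 3 skin toxicity and for hypertension the only conflict is with the general sentence.

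The consequence is that sites may manage the same event differently while each complies with the protocol. In the illustration this is a difference of 12.5 percentage points of planned regorafenib over two cycles (79.2% against 91.7%). That figure describes one assumed patient. It says nothing about how often such patients occur, and it does not show that the section 13.3 review would reach a different result. The primary response analysis is not invalidated. What is affected is dosing after toxicity and the interpretation of dose intensity.

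**What to change.** The clinical team should reconcile four places: the general sentence in section 7.2, footnote c of Table 3, the paragraph after Table 3, and footnote b of Table 4. The revised text should state whether the general rule has exceptions and, for each toxicity and grade, which text governs any return to a higher dose, including its timing and target dose. Which rule is right is a clinical decision and none is proposed here.

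Section 13.3 needs no new calculation rule: dose intensity there compares dose received with dose planned, and a re-escalation rule affects only what is received.

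The cost is a protocol clarification or amendment to wording, with no additional procedures, visits or data.
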